#### Prognostic factors

Several prognostic factors will be investigated at baseline to gain insight into the differences between the intervention and control teams.

##### Sociodemographic measures

Gender (male/female), age (years), Dutch nationality (yes/no), marital status (married/registered partnership/living together; in a relationship/not living together; single/divorced/widow/widower), and the highest educational degree (no schooling completed/primary school; lower vocational education/ secondary vocational education; higher professional education/university) will all be measured at the employee level.

##### Work characteristics

The number of years working for the organization, working days and hours per week, and working at night (yes/no), during the weekend (yes/no) or evenings (yes/no) will all be measured at the employee level.

##### Healthcare consumption

Healthcare consumption is measured at the employee level using the questionnaire on healthcare consumption and productivity loss in patients with a psychiatric disorder (TiC-P) [28]. The number of times the participant consulted a healthcare provider (by phone or visiting during office hours) will be asked using the following questions: “Did you consult (*name healthcare provider*) at any time during the past four weeks?” (“No”/“Yes, … times”), and, if the answer is ‘yes’: “How many times were you in contact with the *healthcare provider* due to depressive complaints?” Healthcare consumption will be measured for the following healthcare providers: general practitioner, physiotherapist, practice nurse mental health, lifestyle counsellor, chiropractor, occupational therapist, exercise therapist, psychiatrist, psychologist, psychotherapist, social worker, and health and safety officer.

##### Co-interventions

We will collect information about all initiatives possibly related to stress prevention@work during the trial period through interviews with stakeholders within the organization.

### Process evaluation

Alongside the effectiveness evaluation, a process evaluation will be conducted. The Nielsen & Randall model for organizational interventions and the Steckler and Linnan framework for process evaluations will be used to gain insight into the implementation process of the SP@W strategy [20, 21]. The criteria described by Steckler and Linnan that are most relevant to the implementation goal are: ‘reach’ and ‘dose received’. Reach is the percentage of intervention teams that participated in SP@W. Dose received will be operationalized as the number of steps of the stepwise DP protocol that are completed. Both reach and dose received will be assessed at the team level. Data for the process evaluation will be collected using questionnaires completed by participants of the intervention teams, interviews with stakeholders, team and stakeholder meeting notes, and DP data logs.

### Sample size

A power analysis has been performed for the main outcome measure: the stress subscale of the DASS-21. This scale has a mean of 4.06 and a standard deviation of 3.81 in a non-clinical sample of North American adults [29]. With a power of 0.80 (1-beta) and an alpha of 0.05, we need 208 participants (104 per group) to demonstrate a relevant effect in the stress scale of 1.5 points. Taking into account a loss to follow-up of 25% after 12 months, a total of 278 employees need to be included.

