### Allocation and matching teams

After the baseline measurement, teams will be matched on their specific work setting (e.g. home-based care or nursing home care) and team size. The aim is to have both comparable teams and an equal number of participants in the intervention and control condition. This information will be obtained from the team coaches. Following the match, allocation to the two conditions will be performed by an independent researcher who does not have information about the perceived stress levels in the teams. After allocation, the teams are informed about the condition they are assigned to: intervention or control (waiting list) condition. A secure login code for the digital platform (DP) for all intervention teams will be sent to the employees responsible for applying SP@W within their team. The use of the DP will be explained during a training by an implementation expert. An invitation for this training will be sent to all responsible employees for the intervention teams. They will also receive an invitation for collaborative learning network meetings and the contact information of all employees responsible for the DP in the intervention teams.

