### Statistical analyses

To investigate the effectiveness of SP@W, all analyses will be performed according to the intention-to-treat principle. Descriptive statistics (means, standard deviations, or frequencies) will be calculated for all measured variables, and will be compared between the intervention and control groups. The effects of SP@W will be analysed by performing a multilevel analysis, while taking into account clustering within teams. A two-tailed significance level of *p* < 0.05 will be considered statistically significant.

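### The sample size of 278 employees makes no allowance for clustering by team, so the stated 80% power does not apply to a trial that allocates whole teams.

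*Protocol article*

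**What the plan says.** The Sample size section (protocol article) bases the trial's size on the primary outcome, the DASS-21 stress subscale. For variability it says: "This scale has a mean of 4.06 and a standard deviation of 3.81 in a non-clinical sample of North American adults". The target is "to demonstrate a relevant effect in the stress scale of 1.5 points", and the result is: "With a power of 0.80 (1-beta) and an alpha of 0.05, we need 208 participants (104 per group) to demonstrate a relevant effect". Allowing for 25% loss to follow-up at 12 months, 278 employees are to be included.

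The design is by team. The Study design section calls it a cluster controlled trial. Under Allocation and matching teams, teams are matched on work setting and size and then allocated as a whole: "After allocation, the teams are informed about the condition they are assigned to: intervention or control (waiting list) condition". The Statistical analyses section adds: "The effects of SP@W will be analysed by performing a multilevel analysis, while taking into account clustering within teams".

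The Sample size section gives no ICC, number of teams, employees per team or design effect. It also claims no gain from baseline adjustment or repeated measurements.

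**The concern.** Employees in one team share a workload, a setting and colleagues, so their stress scores are likely to be correlated. The strategy itself presumes this, because step 2 of its stepwise protocol looks for psychosocial risk factors within a team. When whole teams are allocated, positive correlation raises the variance of the group difference above the value for independent employees. The planned model will include that extra variance; the sample size calculation leaves it out.

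What is at stake is planned power. The analysis accounts for teams, so this omission does not inflate the type I error. But the 80% is the only justification given for the trial's size. A reader of a non-significant result could give it too much weight as evidence against a 1.5-point effect. The Strengths and limitations section also concedes that contamination may reduce the contrast, so there is no power to spare.

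**Working it through.** **Inputs from the protocol.** SD 3.81, difference 1.5, power 0.80, alpha 0.05, equal groups and 25% loss (Sample size; Allocation and matching teams). The test is two-sided (Statistical analyses: "A two-tailed significance level of" 0.05).

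**Step 1: reproduce the stated figure.**

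- Normal approximation: n per group = 2 × (1.960 + 0.842)² × 3.81² / 1.5² = 101.3, so 102.
- t-test: 102.2, so 103.
- Power at the stated 104 per group: 81.0% (normal), 80.7% (t).
- Loss to follow-up: 208 / 0.75 = 277.3, so 278, an exact match.
- A one-sided test would give 80 per group, which does not fit.

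The stated numbers are thus the individual-level calculation, give or take rounding. The slack is 104 / 101.3 = 1.027. A design effect of about 1.03 is the most it could absorb, which at 10 per team is an ICC of about 0.027 / 9 = 0.003.

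**Step 2: add clustering.** With m analysed employees per team:

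- Design effect: DE = 1 + (m − 1) × ICC
- Standard error: SE = 3.81 × √(2 × DE / 104)
- Power = Φ(1.5 / SE − 1.96)
- Difference detectable with 80% power = (1.960 + 0.842) × SE
- Number to include for 80% power: 104 × DE per group, rounded up, doubled, then divided by 0.75

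Worked example with m = 10 and ICC = 0.05: DE = 1 + 9 × 0.05 = 1.45. SE = 3.81 × √(2.90 / 104) = 0.636. Power = Φ(2.358 − 1.960) = Φ(0.398) = 65.5%. Detectable difference = 2.802 × 0.636 = 1.78. Number to include: 150.8 → 151 per group, 302 analysed, 302 / 0.75 → 403.

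The values of m and ICC below are **assumptions**, because the protocol gives neither. All rows have 208 analysed. The t column uses (208/m − 2) degrees of freedom.

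| m | ICC | DE | Power (normal) | Power (t) | Detectable difference | Include for 80% |
|---|---|---|---|---|---|---|
| 5 | 0.01 | 1.04 | 79.5% | 77.5% | 1.51 | 291 |
| 5 | 0.05 | 1.20 | 73.6% | 71.5% | 1.62 | 334 |
| 10 | 0.02 | 1.18 | 74.3% | 69.8% | 1.61 | 328 |
| 10 | 0.05 | 1.45 | 65.5% | 60.9% | 1.78 | 403 |
| 10 | 0.10 | 1.90 | 54.0% | 49.8% | 2.04 | 528 |
| 15 | 0.05 | 1.70 | 58.6% | 51.6% | 1.93 | 472 |
| 20 | 0.10 | 2.90 | 38.5% | 31.5% | 2.52 | 806 |

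Without clustering, 104 per group detects 1.48 points.

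**Step 3: what baseline adjustment could recover.** Adjusting for a baseline score with correlation r multiplies the variance by about (1 − r²), if the reduction is the same between and within teams. At DE 1.45, normal-approximation power becomes 78% with r = 0.5 and 84% with r = 0.6. At DE 1.90 it becomes 66% and 73%. The protocol gives no value of r.

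**The case against.** The strongest reply is that a shortfall in the trial itself has not been shown. Stress is measured at baseline, 6 and 12 months, and a multilevel model can use the earlier scores. At 10 per team and ICC 0.05, a baseline correlation of about 0.54 would restore 80% on the normal approximation. Matching on work setting and team size may also remove some between-team variance if the analysis reflects it. If teams and ICC are both small, almost nothing is lost: 79.5% at 5 per team and ICC 0.01. The size of the problem depends wholly on inputs that the protocol does not give.

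Much of this stands as a limit on size. Actual power cannot be determined from the protocol, and an offset is possible. But the Sample size section claims no such offset, and the Statistical analyses section does not state baseline adjustment. The offset is also less secure with few teams: at DE 1.45 and r = 0.6, power with team-based degrees of freedom is 79.8%.

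It could also be said that a journal article condenses a fuller protocol. That would excuse a missing detail. Here the calculation is shown with its inputs, and it closes without clustering. A fuller document could not add a meaningful ICC and still reach 208 and 278, unless it also used a gain that the article does not mention.

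Finally, employees supply the primary outcome; teams are the unit of allocation and the cluster level in the model. That distinction is correct, and it does not remove the need for a design effect.

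**Conclusion.** The concern holds and must be fixed. The 208 and 278 are correct for individually allocated, independent employees. They do not support 80% power for a team-allocated trial with the planned multilevel analysis, unless the ICC is essentially zero or an unstated gain in precision makes up the loss.

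The likely direction is overstatement; its size is uncertain. Assuming 10 analysed per team and an ICC of 0.02 to 0.10, with no baseline adjustment, power is about 74% down to 54%. Team-based degrees of freedom take off a further 4 to 5 points. On the same assumptions (normal approximation), the difference detectable with 80% power is 1.61 to 2.04 points rather than 1.5. Smaller teams or a lower ICC bring the figure close to 80%; larger teams push it well below.

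**What to change.** Replace the power statement with a clustered calculation that gives:

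- the expected number of teams and of analysed employees per team;
- an ICC range, for example 0.01 to 0.10, with the reason for choosing it;
- the design effect 1 + (m − 1) × ICC, applied before the allowance for loss to follow-up;
- the power for 1.5 points, or the detectable difference, with 278 included and 208 analysed, using degrees of freedom based on the number of teams.

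If the primary model is to adjust for baseline stress, say so under Statistical analyses and show the assumed correlation and the factor (1 − r²) as a separate line.

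The cost is a few sentences and a small table, and a stated power that will probably be less favourable. The correction itself requires no more recruitment and no change of design. If the team wishes to keep 80% power without relying on baseline adjustment, the last column of the table shows the numbers needed under each assumption.

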### Statistical analyses

To investigate the effectiveness of SP@W, all analyses will be performed according to the intention-to-treat principle. Descriptive statistics (means, standard deviations, or frequencies) will be calculated for all measured variables, and will be compared between the intervention and control groups. The effects of SP@W will be analysed by performing a multilevel analysis, while taking into account clustering within teams. A two-tailed significance level of *p* < 0.05 will be considered statistically significant.

## Discussion

This paper described the study protocol of the multifaceted and integral stress prevention strategy, SP@W. It is hypothesized that after a successful implementation of SP@W, the strategy will increase the mean number of work-related stress management interventions implemented within the intervention teams compared to the control teams and lead to a decrease in employee stress over 12 months.

### Strengths and limitations

The first strength of this study is our controlled design. This allows for a comparison between teams within the participating healthcare organization who are exposed to similar environmental conditions that may lead to stress (e.g. organizational changes), if not for access to SP@W. The second strength of this study design is the follow-up period of one year, which allows insight into short-term effects of the intervention after six months and in the longer term after 12 months. Third, by incorporating a process evaluation, we will gain insight into the strategy’s implementation process within the intervention teams. Last, this study will be executed in a real-life setting, which will make it easier to generalize the effects to similar healthcare organizations.

Since SP@W focuses on the organization and not on individual workers, individual randomisation is not feasible. Matching controls may induce bias since matching a limited number of known parameters may lead to differences between teams in the intervention and control group that we are unaware of. Furthermore, we cannot completely rule out contamination since all teams belong to one healthcare organization. A cross-over of information can reduce the contrast between the groups and consequently, the impact of the effects.

### Impact of the results

A combination of several implementation strategies into one integral stress prevention strategy is important to overcome barriers at multiple levels within organizations. SP@W may lead to a reduction of stress and sick leave and an increase in productivity, which is beneficial for employees as well as for the organization.

## Abbreviations

DASS-21: Depression, anxiety and stress scale
DP: Digital platform
HR: Human resource
PSC: Psychosocial safety climate
SP@W: Stress prevention@work
